## 9 Data Management, Statistical Analysis and Record Keeping

## Statistics and Interim Analysis

*The primary research questions for this study are:*

- Does the SMART program, compared with usual care, change health-related quality of life (primary outcome) measured 16-weeks and 12-months following randomisation?

AND

- Does the SMART program, compared with usual care, change peripheral muscle strength, muscle mass, exercise tolerance, exercise adherence and chemotherapy completion rates (secondary outcomes) measured 16 weeks following randomisation?

The analyses for this research question will be performed according to the intention to treat principle. For the primary outcome, health-related quality of life, with 4 assessment points, linear models will be used to account for repeated measures with participant ID entered as a random effect. The primary time point of interest will be the end of the intervention phase. Group, time and group by time will be analysed as fixed effects and the baseline measure will be entered as a covariate to adjust for random baseline differences. Between group difference for the dependent outcome of chemotherapy completion (yes/no) will be analysed using logistic regression. Between group differences for the remaining secondary measures (peripheral muscle force-generating capacity, muscle mass, exercise tolerance) will be examined using linear regression with the corresponding baseline measure used as a covariate. Data transformations or alternative models (such as gamma distribution) will be considered if there is poor model fit.

Missing data will be examined and multiple imputations investigated (assuming they are missing at random). Models will be adjusted for covariates, randomisation variables and confounders such as age. Estimates of the effects will be reported with their corresponding 95% confidence intervals.

*The first secondary research question is:*

- Do factors such as adherence, treatment pathway and cancer stage moderate the magnitude of any change in primary or secondary outcomes? (i.e. moderator analysis)

To understand any moderator effects, the listed covariates will be entered into a multivariable model using the outcomes listed above. In addition, adherence will be examined to see if it mediates the relationship with the outcomes, by calculating the indirect through the use of partial coefficients.

*The second secondary research question is:*

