- What is the health care utilisation, absenteeism and presenteeism over the 12 months following randomisation?

This is an exploratory question and data will be described using mean and standard deviation.

*The third secondary research question is:*

- Does performance on tests of peripheral muscle force-generating capacity and exercise tolerance, change with test repetition (i.e. is there a learning effect)?

This will be assessed using one-way repeated measures analysis of variance (ANOVA). That is, for each participant, data collected over consecutive trials (5 attempts for each measure of muscle force and 2 attempts for the 6MWT) compared to explore if there is an effect of test repetition on these outcomes.

*The fourth secondary research question is:*

What is the minimal detectable difference in health-related quality of life and exercise tolerance?

This will be assessed using anchor-based approach via a Receiver Operating Characteristic curve. This curve will determine the optimal operating point to discriminate between participants who rate themselves as changed vs unchanged at the end of the SMART program.

*The fifth secondary research question is:*

Do psychological determinants of behavioural change, such as capability, opportunity, and motivation affect adherence to the SMART program and physical activity maintenance?

This will be assessed using correlations and a Multiple Regression Analysis of the data from psychological determinant measures (COM-B factors, impairment in functioning, intention, self-efficacy, habit, and mood) across all time-points for each participant. Data from the exit interviews will also be analysed using qualitative methods (such as thematic analysis) to explore participants' reasons for engagement (or lack of engagement).

*The sixth secondary research question is:*

Does the SMART program improve mood, and does mood influence adherence to the program and physical activity maintenance?

This will be assessed using correlations between mood data from the PANAS (across all timepoints) and physical activity engagement.

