## **Sample Size**

Sample size calculation has been conducted using the EORTC QLQ BR-30 (continuous data) as the dependent variable. To detect a difference between the experimental and control groups in this outcome of 8 (which has been estimated as the minimal clinically important difference), assuming a standard deviation of 20.52 (based on previously published literature) (Karsten 2022), with an  $\alpha = 0.05$  and  $1-\beta = 0.8$ , we will need to 104 participants in the experimental group and 104 participants in the control group. In order to account for 20% drop-out, we plan to recruit a sample size of 130 participants in each group. This means we aim to recruit 260 participants over 24 months (recruitment rate of 11 per month).

We believe that this recruitment rate is realistic. This is because, we have recently completed an audit of the RPH Breast Clinic (GEKO number 50167). The Data, Digital and Innovation (DDI) group at RPH compiled information from WEBPAS and showed that 993 adults were treated with surgical breast procedures and/or chemotherapy treatment for BC at the RPH Breast Clinic between 01/07/2021 to 30/06/2023. This is equivalent to 41 people per month. This means that our recruitment fraction for this study will be 27%.

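### Secondary question 6 asks whether SMART improves mood, but the stated analysis only correlates mood with activity and does not compare the arms; the moderator analysis for question 1 names no interaction

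*Protocol*

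**What the plan says.** **Question 6.** Section 9 (Statistics and Interim Analysis) repeats the sixth secondary question from Section 3: "Does the SMART program improve mood, and does mood influence adherence to the program and physical activity maintenance". It has two halves: an effect of the program on mood, and an association of mood with adherence and later activity. One sentence covers both: "This will be assessed using correlations between mood data from the PANAS (across all timepoints) and physical activity engagement".

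**Mood elsewhere.** Section 7 lists mood, measured by PANAS, among the secondary outcomes. The timing-of-outcomes table schedules PANAS before randomisation, mid-way through the intervention, at its end and at 12 months. The between-group regression in Section 9 covers the remaining secondary measures, which are listed in brackets as muscle strength, muscle mass and exercise tolerance. Mood is not in that list.

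**Question 1.** The first secondary question asks whether adherence, treatment pathway and cancer stage moderate the change in outcomes. The plan is: "To understand any moderator effects, the listed covariates will be entered into a multivariable model using the outcomes listed above". It adds that "adherence will be examined to see if it mediates the relationship with the outcomes".

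**The concern.** Whether SMART improves mood is a causal question about a randomised program, and the randomised comparison is what answers it. A PANAS-activity correlation can be strong when the program does nothing for mood, because people who feel better tend to move more. It can also be absent when the program does lift mood, for instance through contact and support rather than through recorded activity. If the plan is followed as written, the report either gives no answer on mood or offers a correlation in place of one. An arm comparison added after the data are seen would no longer be pre-specified.

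For question 1, the coefficient of a factor such as stage, in a model without its interaction with group, says how outcomes differ by stage. It does not say whether the effect of SMART differs by stage. Adherence raises a further difficulty. It arises after randomisation and the program is designed to change it, so it cannot be read as a baseline modifier of the effect.

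**Working it through.** **1. The plan's own figure.** The protocol gives one calculated figure, the sample size, and it is not in dispute. Inputs from the Sample Size section: difference 8, "assuming a standard deviation of 20.52", alpha 0.05 (two-sided assumed), power 0.80.

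- n per arm = 2 × (1.96 + 0.842)² × 20.52² / 8² = 2 × 7.849 × 421.07 / 64 = 103.3, rounded up to 104.
- This matches "104 participants in the experimental group and 104 participants in the control group". Power at 104 per arm is 80.3%, and 104 / (1 − 0.20) = 130.

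**2. Question 6: is there an arm comparison for mood anywhere?**

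| Place in Section 9 | Compares arms? | Includes mood? |
|---|---|---|
| Repeated-measures model (quality of life) | Yes | No |
| Logistic regression (chemotherapy completion) | Yes | No |
| Linear regression (bracketed list of measures) | Yes | No |
| Fifth question: correlations and multiple regression | No | Yes, as a predictor |
| Sixth question: correlations | No | Yes |

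No row has yes in both columns.

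**3. What the correlation can show.** Assumptions not in the documents: no program effect on mood, mood-activity correlation 0.3, 104 per arm, one value per person. In 2,000 simulated trials:

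- the correlation was significant in 99.3%;
- the comparison of arms was significant in 5.2%, which is the nominal error rate.

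An approximate check with Fisher's transformation: atanh(0.3) = 0.310; 0.310 × √(208 − 3) = 4.43; power ≈ Φ(4.43 − 1.96) = 0.993. In this setting the planned statistic is almost always significant although the program does nothing for mood.

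**4. Question 1: covariate or interaction?** The quality-of-life model names the interaction of group with time explicitly. The moderator sentence names no interaction. Treatment pathway is a stratification factor, and Section 9 already adjusts models for randomisation variables. For pathway, entering it as a covariate therefore adds nothing to the main model.

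Illustration, with an assumed 50:50 factor, effects of +8 and −8 in its two levels, SD 20.52 and 104 per arm. A model with group and the factor as main effects flags a group effect in about 6% of runs and has no term for the difference between levels. The interaction test detects it in about 79%.

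**5. Why the interactions should be labelled exploratory.** Same assumptions, no baseline adjustment:

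- SE of the main effect = 20.52 × √(2/104) = 2.85.
- SE of the interaction = 2 × 2.85 = 5.69 (from unrounded values).
- Difference between levels detectable with 80% power = 2.80 × 5.69 = 15.9 points.
- Power for an 8-point interaction = Φ(8/5.69 − 1.96) = Φ(−0.55) = 0.29.

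The protocol claims no power for moderation, so this contradicts nothing it states. It bears only on how the result should be labelled.

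**The case against.** **Too broad a reading.** A reader might infer that neither question is answered and that no randomised contrast is present. The documents do not support that.

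- The correlation does bear on the second half of question 6, as association. For maintenance it does so only as far as activity is recorded; the timing table schedules exercise participation during the intervention phase alone.
- For question 1, the moderators go into models for the outcomes already listed, and those models contain group. What is unstated is the interaction, not the group contrast.

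**Detail for the SAP.** The protocol calls question 1 a moderator analysis and says a final SAP will be published. Writing out interaction terms is ordinary SAP work, and the text does not say that factors enter only as main effects. This objection has weight and is why question 1 is the lesser point. It does not reach the first half of question 6. There the protocol does not leave the method open; it fixes one that does not match the question.

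**Repeated rows.** Because the fifth question uses data "across all time-points for each participant" and the sixth uses all timepoints, a reader might infer that several rows per person are treated as independent and that false positives are inflated. The text does not say so. Separate correlations at each time point, or per-person summaries, fit it equally well, so no error-rate claim is made here.

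**Importance.** These are secondary questions, and the data will be collected in any case. That is accepted and limits the severity.

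**Conclusion.** The point holds for the first half of question 6. As written, the plan contains no comparison of SMART with usual care on mood, although mood is a secondary outcome measured at four time points. This conclusion rests on reading the text and needs no numerical assumption. The 99% against 5% contrast illustrates it under an assumed correlation of 0.3.

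For question 1 a smaller point holds. The interaction of group with each factor should be stated, and adherence should not serve as both moderator and mediator. The figures given for moderation rest on an assumed 50:50 factor and no baseline adjustment. Treatment pathway is not described as such a split, so they indicate scale only.

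Severity is moderate. The primary endpoint, its model and the sample size of 104 per arm (130 with drop-out) stand. A wrong or missing answer would be confined to secondary questions 6 and 1.

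**What to change.** **Question 6.** Replace the single sentence with two.

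- First half: analyse PANAS positive affect and negative affect, each with the repeated-measures model already planned for quality of life (baseline PANAS as covariate; group, time and their interaction as fixed effects; participant as random effect). Report the SMART minus control difference at 16 weeks with a 95% confidence interval, as a secondary result.
- Second half: keep the correlation of PANAS with activity, labelled as association.

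**Question 1.** State that interactions of group with treatment pathway and of group with cancer stage will be estimated, and label them exploratory. Remove adherence from the moderators and keep it in the mediation analysis only.

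**Cost.** A few lines in the protocol and SAP and a few extra model runs on data already scheduled. There are no new assessments and no change to the sample size. The change should be made before any mood results by arm are seen, so that the comparison counts as pre-specified. If the SAP already contains these analyses, the protocol text only needs to be brought into line.

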### 3 Trial Aims / Objectives / Hypotheses

For all research questions, the study population refers to adults with newly diagnosed with breast cancer who are undergoing treatment through the Breast Clinic at RPH.

Primary research questions:

- 1) Does the SMART program, compared with usual care, change health-related quality of life (primary outcome) measured 16-weeks and 12-months following randomisation?
- 2) Does the SMART program, compared with usual care, change peripheral muscle strength, muscle mass, exercise tolerance, exercise adherence and chemotherapy completion rates (secondary outcomes) measured 16 weeks following randomisation?

Secondary research questions:

- 1) Do factors such as adherence, treatment pathway and cancer stage moderate the magnitude of any change in primary or secondary outcomes? (i.e. moderator analysis)
- 2) What is the health care utilisation, absenteeism and presenteeism over the 12 months following randomisation? (descriptive analyses only, to guide patient expectations in regarding these outcomes)

- 3) Does performance on tests of peripheral muscle force-generating capacity and exercise tolerance, change with test repetition (i.e. is there a learning effect)? (can be answered by Honours students enrolled in the BSc physiotherapy at Curtin University)
- 4) What is the minimal detectable difference in health-related quality of life and exercise tolerance? (can be answered by Honours students enrolled in the BSc physiotherapy at Curtin University)
- 5) Do psychological determinants of behavioural change, such as capability, opportunity, and motivation affect adherence to the SMART program and physical activity maintenance?
- 6) Does the SMART program improve mood, and does mood influence adherence to the program and physical activity maintenance?

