### 7) Optimisation of behaviour change technique use

An online digital workshop will contain advice for participants on identifying and effectively using behaviour change techniques based on the Behaviour Change Taxonomy (Michie et al., 2013); for example, action planning, problem solving, and habit formation. Additional booster sessions (over phone or telehealth) will also be available to participants, if appropriate.

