## OTHER VARIABLES

**Descriptive variables** will be recorded such as age, sex, body mass index, employment status, co-morbid conditions, stage of cancer and details of cancer treatment.

**Healthcare utilisation and adherence with exercise** will be assessed in both groups. In the control group, this will be documented during the monthly phone calls and exercise diaries. In the experimental group, this will be monitored by asking each participant during the weekly supervised sessions and also using exercise diaries (see Section 4, Monitoring). Regarding healthcare utilisation, we will ask each participant to recall the number of; (i) visits to the Emergency Department, (ii) inpatient admission days, (ii) outpatient appointments and, (iii) visits to any other healthcare provider (Y/N, who, number of visits). Regarding adherence with exercise, we will ask each participant to recall the number of minutes spent engaging in moderate or vigorous intensity exercise and details regarding any resistance exercise.

**Absenteeism and presenteeism** will be assessed using the iMTA productivity cost questionnaire (Bouwman 2015).

**Global rating of change** will be assessed by asking participants, on completion of the SMART exercise program, to indicate if their health-related quality of life or exercise tolerance had 'improved', 'worsened' or 'stayed the same'. Those participants who rated their walking ability as 'improved' or 'worsened' will then be asked to rate the degree of change on a seven-point scale (1 a little better to 7 a great deal better).

**Feasibility and acceptability** will be measured using; (i) Quantitative data from an acceptability and feasibility questionnaire, and (ii) qualitative data from exit interviews. These are described below:

*Quantitative data* will be collected using a questionnaire asking participants to rate their perceptions of the SMART exercise program (e.g., "*I thought the SMART exercise program was easy to understand*"). Participants can rate each item on a five-point scale (1 "*I don't agree at all*" to 5 "*I totally agree*"). Four open-ended items at the end of this questionnaire allow participants to include additional feedback (e.g., "*What did you like about the SMART exercise program?*").

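### Secondary questions 5 and 6 relate exercise to mood and psychological determinants with no term for randomised group and no stated arm, so an association pooled over both arms could partly be the SMART-versus-control difference

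*Protocol*

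**What the plan says.** Secondary question 6 (Protocol, section 3) asks: "Does the SMART program improve mood, and does mood influence adherence to the program and physical activity maintenance". Under Statistics and Interim Analysis, the only analysis given for it is "correlations between mood data from the PANAS (across all timepoints) and physical activity engagement".

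Question 5 asks whether psychological determinants "affect adherence to the SMART program and physical activity maintenance". The method is: "This will be assessed using correlations and a Multiple Regression Analysis of the data from psychological determinant measures". The measures are listed as "COM-B factors, impairment in functioning, intention, self-efficacy, habit, and mood) across all time-points for each participant". Randomised group is not on that list, and neither method says whether one arm or both are analysed.

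Other sections bear on this:

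- Section 7 and its timing-of-outcomes table have all participants complete the questionnaires. Other Variables says that adherence with exercise "will be assessed in both groups". Selection of participants for analyses puts everyone randomised into the final analyses.
- For the primary outcome, the same statistics section is explicit: "Group, time and group by time will be analysed as fixed effects".
- A further sentence there adjusts models for covariates, randomisation variables and confounders such as age. It stands under the primary research questions and does not name the randomised group.
- SMART's stated target is weekly exercise (Intervention/Product Description, item 1). Item 7 adds a workshop on "identifying and effectively using behaviour change techniques", with action planning, problem solving and habit formation as examples.

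**The concern.** In a two-arm trial, allocation is a potential common cause of anything the intervention changes. SMART is meant to raise exercise. It may also raise habit or planning scores, and question 6 itself entertains an effect on mood. If both variables sit higher in one arm, pooling the arms produces a correlation even when, within each arm, a person's mood says nothing about how much that person exercises.

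The questions are worded causally (affect, influence). The Publication section lists the effects of individual differences in these determinants among the most important expected findings. A pooled correlation cannot separate such individual differences from the contrast between arms, and the arm component grows as SMART becomes more effective.

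**Working it through.** **1. The plan's own figure.** The protocol gives no calculation for questions 5 or 6, only for the primary outcome: difference 8, SD 20.52, alpha 0.05 (two-sided assumed), power 0.80.

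n per arm = 2 × (1.960 + 0.842)² × (20.52/8)² = 103.3, rounded up to 104. Allowing for 20% drop-out, 104/0.8 = 130. Both figures match the protocol. The totals used below are N = 208 (completers) and N = 260 (recruited). The planned standardised effect is 8/20.52 = 0.39 SD.

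**2. Correlation induced by pooling.** Take two equal arms (allocation is 1:1), zero correlation within each arm, and SMART shifts of d1 (mood or determinant) and d2 (exercise) in within-arm SD units. Then

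r = (d1·d2/4) / √[(1 + d1²/4)(1 + d2²/4)].

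For example, d1 = 0.4 and d2 = 0.8 give 0.08/√(1.04 × 1.16) = 0.073. If d1 = 0, as expected for a score taken before randomisation, r = 0.

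**3. Chance of p < 0.05.** By the Fisher z approximation, with s = atanh(r)·√(N − 3), the rejection probability is 1 − Φ(1.96 − s) + Φ(−1.96 − s). For 0.4/0.8 at N = 208, s = 0.0730 × 14.32 = 1.045, which gives about 18%.

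The shifts below are assumptions. The 0.39 is borrowed from the planned quality-of-life effect.

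| Mood/exercise shift (SD) | Induced r | N = 208 | N = 260 |
|---|---|---|---|
| 0.2 / 0.5 | 0.024 | 6.4% | 6.7% |
| 0.39 / 0.39 | 0.037 | 8.2% | 9.0% |
| 0.39 / 0.8 | 0.071 | 17.5% | 20.7% |
| 0.5 / 1.0 | 0.108 | 34.4% | 41.5% |

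**4. Check by simulation.** With one value per person, N = 208 and 3,000 runs, the four rows gave 5.5%, 8.7%, 17.1% and 33.8%. A separate run of 4,000 trials at 0.4/0.8 gave 19%.

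**5. After the change.** In the same 3,000-run simulations, for shifts from none up to 0.8/1.2 SD, adjusting for group gave 3.8% to 5.1%. Restricting to the SMART arm gave 4.7% to 5.3%. Both are nominal.

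**6. Limits.** These figures concern a single bivariate correlation. They do not describe the multi-predictor regression in question 5, and they include no effect of repeated visits.

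**The case against.** **Pooling is implied, not stated.** No sentence says the arms are combined. Controls have no programme to adhere to, so the adherence half of both questions, read literally, uses the SMART arm only, and this confounding cannot arise there. That stands. A reader might infer that question 6 must pool the arms because it also asks whether SMART improves mood. That does not follow, since a mood-by-activity correlation compares no arms on either reading. Pooling is suggested instead by data collection in both arms, by the inclusion of everyone randomised, and by an outcome worded as activity engagement rather than SMART adherence.

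**It may be detail for the analysis plan, and the adjustment sentence may cover it.** A published analysis plan is promised, and the adjustment sentence might be read as reaching the question 5 regression. That is possible, so the point is weaker for that regression. Its most natural meaning is the stratification factors, however, and it cannot adjust a simple correlation, which is the only method stated for question 6.

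**The effect may be small.** A reader might infer that whenever SMART shifts both variables the trial will report a false driver of exercise. The documents do not support that. They give no shifts, the Background calls exercise effects modest, and modest shifts give only 6 to 8% against a nominal 5%. Nor do the Background or workshop item name mood or motivation as something SMART is built to change. They speak of goal setting, social support, planning, coaching, problem solving and habit formation.

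**There is little maintenance data to distort.** The timing table marks participation in exercise only weekly during the intervention phase, with nothing at 12 months. That stands too. The practical exposure is in exercise recorded during the intervention, related to scores taken midway or at its end. A group term would not fill a gap in later exercise data.

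**Conclusion.** The concern holds in a limited form. As written, questions 5 and 6 carry no randomised-group term and no restriction to one arm. If the arms are pooled and SMART moves both variables, part of any association with physical activity engagement or maintenance can be the between-arm difference. It is clearest for question 6.

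The size depends on assumed shifts. It is close to negligible at 0.2/0.5 or 0.39/0.39 SD, about three to four times the nominal error rate near 0.4/0.8, and about seven times at 0.5/1.0. This assumes no association within arms, one value per person and 208 participants. Severity is minor to moderate and confined to secondary questions.

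**What to change.** Under Statistics and Interim Analysis, for questions 5 and 6:

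- (a) State that adherence to the SMART program is analysed within the SMART arm only.
- (b) Where both arms are used, for activity engagement or maintenance, add randomised group to the regression and report group-adjusted (within-arm) correlations.
- (c) Word the results as associations. A group term removes only the between-arm component. Exercise may still improve mood rather than the reverse.

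The cost is one degree of freedom for (b) and some wording; no data collection changes. For (a) the sample is about half, 104 instead of 208. The correlation detectable with 80% power at two-sided 5% follows from atanh(r) = (1.960 + 0.842)/√(N − 3). It rises from about 0.19 (2.802/14.32 = 0.196) to about 0.27 (2.802/10.05 = 0.279).
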